### Survey sites

The survey has been developed and is coordinated by the Saxony Center for Feto/neonatal Health (SCFNH) at the Medical Faculty of TU Dresden. All hospitals where care is provided to newborns according to one of the levels of neonatal care defined by the American Academy of Pediatrics or a similar regional equivalent are eligible to participate, regardless of location and size.

The enrolment of hospitals is possible from 1st of March 2022 onwards. After successful enrolment, the participating hospitals will collect data over a period of 6 months. A follow-up to the study is not planned. Participating sites will be considered to have completed the survey-period when they have provided the data collected over 6 months to the common database.

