### Objectives

The overall aim of this survey is to estimate the frequency of various interventions applied to newborn infants in the DR and to investigate the impact of possible influencing factors such as centre size and location, level of neonatal care, working hours and weekly periods.

The main objectives of this study are:
1.To estimate the total frequency of interventions given to neonates in the DR in order to support neonatal transition and to compare this estimate with prior data.2.To estimate the frequency of single supportive interventions applied to neonates in the DR.3.To investigate the impact of the following patient-specific factors on supportive interventions:
a.gestational age (separated into different gestational age groups)b.mode of birth (c-section vs. vaginal delivery)4.To investigate the impact of the following structural factors on frequency of single interventions:
a.Designated level of neonatal care according to the definition of the American Academy of Pediatrics (AAP) (15)b.Centre size (defined by total number of newborn infants in 2021)c.Presence of trained neonatologists 24/7d.Centre location (defined by country)5.To investigate the impact of the following organisational factors on frequency of supportive interventions:
a.Weekly period of birth (Monday–Friday vs. weekend)b.Daily period of birth (00.00–08.00, 08.00–16.00, 16.00–00.00)Further objectives include:
6.To further elucidate the mode of respiratory support by analysing the combined frequency of the use of CPAP, non-invasive ventilation and invasive ventilation, and by analysing the frequency of primary intubation (without application of non-invasive respiratory support).7.To generate current data regarding surfactant administration in the DR by comparing the frequency of less-invasive surfactant administration versus application *via* endotracheal tube.8.To investigate the frequency of laryngeal mask use as an alternative airway management tool in the DR.9.To further elucidate the current practice regarding the route of drug administration by comparing the frequency of peripheral venous, umbilical venous and intra-osseous access in the DR.10.To evaluate certain indicators of adherence to ERC guidelines (e.g., oxygen supplementation in resuscitation of early pre-term infants).

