### Sample size

The targeted sample size was decided upon empirically. The rarest described intervention in the literature is the administration of epinephrine with a frequency of as low as 0.05% and we wanted to collect data on at least 20 infants receiving this intervention. Therefore, the calculated total number of births during the study period must equal or exceed 40,000. We expect at least 500 births per participating hospital during the study period, leading to a target of 80 participating hospitals. Assuming an intervention rate of 10%, this results in a sample size of 4,000 infants receiving interventions. As we wish to be able to strive to have meaningful comparisons between different levels of neonatal care and different healthcare systems, we are looking to include hospitals from 20 countries and if possible multiple hospitals of different neonatal care levels per country. Ideally, this would mean 4 hospitals per country, one per level of neonatal care. Participating hospitals will be recruited *via* direct contact, referrals by other hospitals and presentation of the study protocol at scientific congresses.

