Peripheral i.v. access	Placement of peripheral IV access regardless of administration of fluids/drugs
Umbilical venous access	Placement of umbilical venous access regardless of administration of fluids/drugs
Intraosseous access	Placement of intraosseous access regardless of administration of fluids/drugs
Chest compressions	Administration of chest compressions at least for one cycle (three compressions) according to ERC guidelines
Adrenaline	Administration of adrenaline at least once, regardless of administration route

Additionally, the following baseline characteristics are collected for every survey site:
•Designated level of neonatal care according to the definition of the AAP (15)•Total births per year (historical data from 2021)•Number of admissions to the neonatal intensive care unit (either in-house or nearest available) per year (historical data from 2021)•Total number of infants born per month during the survey period•Total number of infants born per month *via* c-section during the survey period•Permanent availability of a trained neonatologist either in-house or on call

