## Discussion

Supporting postnatal transition of neonates seems to be the most frequently performed medical intervention (3). National and international guidelines are regularly updated in order to recommend an evidence based approach towards neonatal life support (17). However, data on the frequency of different interventions is scarce, outdated and often localized and therefore not representative for different health care systems or levels of care.

This international and multi-centre survey will provide much needed data on the frequency with which interventions are currently applied in the DR. Furthermore, the survey will examine the influence of different factors on administered interventions. Thereby, it will not only provide up-to-date information for future guidelines but will also help to generate hypotheses for further research and designing future studies on DR-management.

Current guidelines recommend different interventions in order to support postnatal transition, with a special focus on respiratory support (17). As a result, non-invasive positive pressure ventilation is a relatively common intervention with described frequencies ranging from 4% to 12% of all neonates (14, 18). Other interventions like the administration of chest compressions or epinephrine are much rarer at described frequencies from 0.1% up to 0.3% (3, 18) and 0.05% to 0.3% (14, 19) respectively. However, little is known for other interventions.

Video recordings of neonatal resuscitation represent a possible solution to track performed interventions (20). By detailed analysis of video recordings, certain DR-interventions in preterm and term infants after c-section were previously described both for a single centre and as a comparison between different centres (21–23). However, this data is not representative for all infants.

The multi-centre and international approach of surveying current DR-management allows a comparison across centres of different sizes, levels of neonatal care and health care systems. The survey is easy to perform and not very time consuming, thus it is easy for hospitals to participate, ensuring large data sets. The prospectively planned stratification into different subgroups will provide detailed information for certain risk groups. Comparison of data from different countries will disclose variations that could be due differences in local guidelines, recommendations and practices.

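### Objective 10 evaluates adherence to ERC guidelines at hospitals recruited worldwide, but the listed site items do not record which guideline each hospital follows

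*Protocol article*

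**What the plan says.** Under Survey sites, hospitals that care for newborns at one of the AAP levels or a regional equivalent "are eligible to participate, regardless of location and size". No eligibility condition concerns the resuscitation guideline a hospital uses. Under Sample size, the sponsor writes "we are looking to include hospitals from 20 countries".

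Objective 10, the last of five further objectives, is "To evaluate certain indicators of adherence to ERC guidelines". The one example given is oxygen supplementation in early preterm infants. The objective does not say at which hospitals adherence is to be evaluated.

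The Discussion accepts that guidelines may vary: "Comparison of data from different countries will disclose variations that could be due differences in local guidelines, recommendations and practices".

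Under Study variables, the site-level list opens with "Additionally, the following baseline characteristics are collected for every survey site". It has six items: designated level of care, births in 2021, neonatal intensive care admissions in 2021, monthly births, monthly caesarean births, and lastly "Permanent availability of a trained neonatologist either in-house or on call". Neither this list nor the infant-level list asks which guideline the hospital follows.

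**The concern.** Adherence presupposes that the hospital has adopted the guideline it is measured against. In a survey open to all countries, some hospitals may work to a different guideline. If that guideline departs from ERC on the indicator chosen, an infant managed exactly as the hospital intends will not meet the ERC indicator. In the data, that infant looks the same as one at an ERC hospital whose team did not follow ERC.

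What is at stake is how objective 10 can be read. A low figure might mean that ERC is poorly followed where it applies, or that it does not apply at some of the hospitals. These call for different responses, and the listed variables do not distinguish them. The limitations set out in the Discussion cover order and intensity of interventions, indication, maternal confounders and under-reporting, but not this.

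**Working it through.** **Scale of the survey.** The plan's own figures reproduce, and the point does not affect them.
- Births: 20 infants given epinephrine / 0.0005 = 40,000.
- Hospitals: 40,000 / 500 births each = 80, which agrees with 20 countries × 4 hospitals = 80.
- Infants receiving interventions: 40,000 × 0.10 = 4,000.

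A question put once to each hospital therefore yields about 80 answers.

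**The sections side by side.**
1. Survey sites and Sample size: no geographic limit, 20 countries.
2. Discussion: local guidelines are named as a possible source of variation between countries.
3. Objective 10: ERC is the only yardstick, with no restriction to ERC hospitals.
4. Study variables: the guideline in force is in neither the site list nor the infant list.

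Taken together, the plan expects the guideline to vary, measures against one guideline, and does not list the variable that would tell the two situations apart.

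**When it matters.** For one indicator, let
- s = share of the relevant infants at hospitals following a guideline other than ERC;
- d = share of those infants whose hospital's guideline differs from ERC on this indicator;
- a = proportion meeting the indicator where the local guideline agrees with ERC on it;
- b = proportion meeting it where the local guideline differs.

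The pooled proportion is P = (1 − s·d)·a + s·d·b, so a − P = s·d·(a − b).

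- If s = 0 (all hospitals follow ERC) or d = 0 (the other guidelines agree with ERC on the indicator), then P = a and there is no effect.
- If s·d > 0 and b < a, P lies below a, and the gap reflects the choice of guideline, not departure from one.

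The documents give no value for s, d, a or b. The effect can be zero or more, and no figure can be derived from the article.

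**Can the existing data stand in?** Country is an analysis factor (objective 4d and Table 2), so the indicators can be split by country. That requires assigning a guideline to each country by assumption, and it fails where hospitals within a country differ. It is a partial proxy.

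**The case against.** Much of the case on the other side stands.

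- A reader might infer that hospitals using another guideline automatically count as non-adherent. The documents do not support this. They give no scoring rule, and such a hospital would fall short only where its guideline differs from ERC on the indicator. Nothing in the article shows that any guideline differs on the one indicator it names.
- A reader might infer that these hospitals could never be separated afterwards because centres are pseudonymised. That is not so. Under Data collection and management, only patient data are anonymised; centres receive an ID, send forms monthly and are queried about missing or unclear data. Individual feedback to each hospital is also planned. The information can still be obtained.
- A reader might extend the point to the country comparison in objective 4d. The article does not claim to separate guideline effects from practice effects there. It says variation could be due to local guidelines, and it states that no causal relationships can be analysed.
- Table 2, the minimum list of results, contains no adherence figure, so a pooled one is possible but not promised. If the aim is how often practice anywhere matches ERC, the pooled proportion is a valid answer to that question and only the word adherence is wrong.
- The site list may not be exhaustive: country is analysed but not listed there, and the Data Collection Form is not shown.

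The last two arguments narrow the point without removing it. Objective 10 is worded as adherence and is not limited to ERC hospitals, and the article's explicit site list has no guideline item. A later analysis cannot supply that information unless someone asks for it.

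**Conclusion.** The point holds as a cheap improvement. As the article is written, objective 10 cannot distinguish departure from ERC from use of another guideline at any hospital whose guideline differs from ERC on the indicator. A result pooled over all sites should therefore be read as concordance with ERC.

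The size is unknown. It depends on how many infants come from hospitals with a diverging guideline and on how far practice there differs. The conclusion assumes that some participating hospitals do not follow ERC, which open eligibility and the Discussion make plausible but do not establish. It also assumes that the unseen form has no guideline item.

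The reach is limited to objective 10. Objectives 1 to 5, the frequency estimates and the sample size are unaffected.

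**What to change.** 1. Add one site-level question: which neonatal resuscitation guideline was in force at the hospital during its survey period (ERC, another named guideline, or a local protocol). Hospitals already enrolled can answer it retrospectively through the existing queries to sites.
2. Report objective 10 as adherence only for hospitals that state they follow ERC.
3. Report the same indicators for the other hospitals separately, labelled as practice or concordance with ERC. Hospitals that cannot answer belong in this group, marked as unknown.

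The cost is about 80 short answers and fewer infants in the adherence analysis; how many fewer will be known only once the answers are in. Data collection on infants does not change.

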### Study variables

For every included neonate the following data are collected:
•Weekly period of birth (Mo–Fr/Weekend)•Time period of birth (8:00–16:00/16:00–0:00/0:00–8:00)•Completed week of gestation•Mode of birth (c-section/no c-section)•Application of the following items during neonatal resuscitation:
○Respiratory support:
◾ Initial inflations◾ CPAP◾ Non-invasive ventilation◾ Oxygen supplementation○Airway management:
◾ Suction*◾ Laryngeal mask◾ Endotracheal intubation + invasive ventilation○Drug application:
◾ Surfactant administration (*via* endotracheal tube)◾ Less-invasive Surfactant administration (LISA)◾ adrenaline◾ Caffeine○Vascular access
◾ Peripheral IV access*◾ Umbilical venous access◾ Intraosseous access○Chest compressions (if performed at least once)Marked items (*) will only be recorded if performed together with other interventions due to practicability aspects. Tactile stimulation is not recorded because while it is most likely applied to every neonate, the management varies widely between centres and there exists no consensus on the most effective stimulation method (16).

For detailed definitions of the variables see Table 1.

**Table 1 T1:** Definitions of study variables/data collection form items.

Study variable	Definition
Initial inflations	Positive pressure application using a facemask (at least ≥10 cm H_2_O over PEEP) over at least 2 s at least once before any other respiratory support
CPAP	Continuous positive pressure application (≥5 cm H_2_O) with sufficient device positioning and regardless of interface and pressure driver
Non-invasive ventilation	Intermittent positive pressure ventilation (iPPV) at least two times in a row regardless of interface and pressure driver; initial inflations excluded
Suction	Use of any suction device for airway clearance
Laryngeal mask	Insertion of laryngeal mask as airway device
Oxygen supplementation	Application of any additional oxygen, FiO_2_ > 0.21
Intubation + invasive ventilation	Ventilation *via* endotracheal tube (ETT); not to be ticked if intubation was used as mean for surfactant administration and the infant was extubated prior to the end of neonatal resuscitation
Surfactant *via* ETT	Surfactant administration *via* endotracheal tube, regardless of continuation of invasive ventilation after Surfactant administration
Less-invasive surfactant administration	Any other form of Surfactant administration less invasive than *via* endotracheal tube
Peripheral i.v. access	Placement of peripheral IV access regardless of administration of fluids/drugs
Umbilical venous access	Placement of umbilical venous access regardless of administration of fluids/drugs
Intraosseous access	Placement of intraosseous access regardless of administration of fluids/drugs
Chest compressions	Administration of chest compressions at least for one cycle (three compressions) according to ERC guidelines
Adrenaline	Administration of adrenaline at least once, regardless of administration route

Additionally, the following baseline characteristics are collected for every survey site:
•Designated level of neonatal care according to the definition of the AAP (15)•Total births per year (historical data from 2021)•Number of admissions to the neonatal intensive care unit (either in-house or nearest available) per year (historical data from 2021)•Total number of infants born per month during the survey period•Total number of infants born per month *via* c-section during the survey period•Permanent availability of a trained neonatologist either in-house or on call

### Data collection and management

All survey sites will collect the observational data prospectively into the provided Data Collection Form (see Attachments), either in paper or electronic form. Data missing due to documentation errors can be obtained by retrospective chart review. The completed Data Collection Form will be sent electronically on a monthly basis to the SCFNH for entry into the central database (CD). If assigned, local patient IDs will be removed before transferral to the SCFNH in order to provide full anonymization in the CD. All survey sites will receive an ID for center pseudonymization before being included in the CD. The CD will be stored password-protected locally within the SCFNH and can only be accessed by members of the study team. As the data is collected in an anonymized way, no separate consent form is obtained. Possibly missing/unclear data will be requested from the participating hospitals. In case the requested data cannot be provided, the respective data will be marked and not included in statistical analysis.

### Data analysis

Data will be analysed globally and for specific, predefined subgroups for every independent variable (e.g., completed week of gestational age, mode of birth, designated level of neonatal care).

Descriptive analysis will be performed on all study variables including absolute numbers and percentages as well as median and range for numerical variables. For all observed interventions confidence intervals will be calculated on a confidence level of 0.95. Additionally, statistical analysis regarding possible correlations will be performed on all study variables using phi coefficient and chi square test of independence. Statistical analyses and graphical presentations will be performed using R (The R Foundation for Statistical Computing, Vienna, Austria).

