### Study population/inclusion and exclusion criteria

Supportive DR-interventions are surveyed for all neonates who fulfil the following criteria:
◾ born in a participating hospital during the 6-month survey period◾ receive supportive interventions more than basic drying or tactile stimulation during the first 30 min of lifeNeonates are excluded based on the following criteria:
◾ neonates receiving only suction or peripheral venous access without any other supportive intervention◾ neonates requiring supportive interventions only after the first 30 min of life.

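### If pairs of interventions are tested for independence on the individual records, the entry rule depletes the both-absent cell and biases phi downward

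*Protocol article*

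**What the plan says.** The Data analysis section of the protocol article states that "statistical analysis regarding possible correlations will be performed on all study variables using phi coefficient and chi square test of independence". The Study variables section lists the yes/no interventions (CPAP, non-invasive ventilation, oxygen, intubation, surfactant, adrenaline and others) among those variables. No denominator is given for a table that crosses one intervention with another.

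The inclusion criteria create an individual record only for an infant who received more than drying or tactile stimulation in the first 30 minutes. They exclude "neonates receiving only suction or peripheral venous access without any other supportive intervention". The Study variables section adds for suction and peripheral IV access: "Marked items (*) will only be recorded if performed together with other interventions due to practicability aspects".

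Untreated births enter only as site totals, under the item "Total number of infants born per month during the survey period", with a matching count for c-sections.

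Table 2, described as a minimum, lists differences in intervention frequency between subgroups. It names no pair of interventions. It restricts a comparison to treated infants in one place only, the gestational-age comparison.

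**The concern.** A chi-square test of independence on a pair of interventions asks whether the two are unrelated. In a database that an infant enters only by receiving an intervention, an infant who lacks one item must have another. Two items that are unrelated across births are then negatively related among the records. A larger sample does not help; it only makes the artefact more significant.

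A negative phi between two common items, such as CPAP and non-invasive ventilation, reads as one replacing the other. The Discussion offers the survey as input to guidelines and to new hypotheses, so an artefact of that kind could be taken up as a finding. The limitations mention that order and causal influence between interventions cannot be seen. They do not mention this selection effect.

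**Working it through.** **The plan's own figures.** The rarest item is at 0.05% and the authors say "we wanted to collect data on at least 20 infants receiving this intervention": 20 / 0.0005 = 40,000 births. 40,000 / 500 per hospital = 80 hospitals. 40,000 x 0.10 = 4,000 treated infants. All three reproduce.

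**Inputs.** From Sample size: N = 40,000 births and n = 4,000 included infants. From Discussion: non-invasive ventilation 4% to 12% (4% is used, since 12% cannot stand beside a 10% total), chest compressions 0.1% to 0.3%, adrenaline 0.05% to 0.3%. Assumed: the 5%, 1% and 2% items, every joint frequency, and a significance level of 0.05, because none is stated for the tests.

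**Formulas.** Let A and B be the numbers of infants with each item and a the number with both; b = A - a, c = B - a, and d = table total - a - b - c. Then phi = (ad - bc) / sqrt(product of the four margins), and chi-square = table total x phi squared, 1 df. For unstarred items, a, b and c are the same in both tables. Only d changes, by 40,000 - 4,000 = 36,000.

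**Common pair, 4% and 5%, independent across births.** A = 1,600, B = 2,000, a = 1,600 x 2,000 / 40,000 = 80, b = 1,520, c = 1,920.
- All births: d = 36,480, phi = 0.
- Included infants: d = 480, phi = (80 x 480 - 1,520 x 1,920) / sqrt(1,600 x 2,400 x 2,000 x 2,000) = -2,880,000 / 3,919,184 = -0.735, chi-square = 2160.

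**Same pair with increasing joint use.**

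| Joint use relative to chance | phi, all births | phi, included infants |
|---|---|---|
| 1x | 0 | -0.735 |
| 3x | +0.094 | -0.571 |
| 8x | +0.328 | -0.163 |
| 10x | +0.42 | 0 |
| 15x | +0.656 | +0.408 |

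**Where the sign turns.** Among included infants, ad - bc = a x n - A x B, which is negative when a < AB/n. Chance across births is AB/N, so the limit is N/n = 40,000 / 4,000 = 10 times chance. For the 5% and 15% treated rates in the Abstract, the limit is 1/0.05 = 20 and 1/0.15 = 6.7 times.

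**Less common items, independent across births.** Both at 2%: phi -0.225, chi-square 203. Both at 1%: phi -0.10, chi-square 40. Ventilation 4% with compressions 0.1%: phi -0.074, p = 0.000003.

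**Where the effect is small or absent.**
- Compressions 0.1% with adrenaline 0.05%, independent: phi -0.006, p = 0.69. At 0.3% each: phi -0.028, p = 0.078.
- The same pair with 18 of 20 adrenaline infants also compressed (assumed): phi +0.634 among included infants, +0.636 across births.
- Ventilation with compressions, 80% of compressed infants ventilated (assumed, 20 times chance): phi +0.082 among included infants.

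**Is the all-births table the right one?** Take two items each given to half of treated infants and independent among them: 5%, 5%, joint 2.5%. Across births phi = (0.025 - 0.0025) / (0.05 x 0.95) = +0.47. This comes only from both items being used in infants who need support.

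**Starred items.** Infants with suction or peripheral IV access alone leave no record, so their single-item cell is short as well as d. Birth totals cannot repair that table, and the direction of its bias cannot be derived from the document.

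**The case against.** The strongest reply is that the plan may never run these tests. None of the ten objectives asks how one intervention relates to another, Table 2 lists no pair, and the Data analysis section opens by framing the work around independent variables such as gestational age and level of care. In that context the correlations may be factor by intervention. This reply stands in part: intervention pairs are covered by the literal wording, not by a listed analysis. But Table 2 is only a minimum, the text fixes both the statistic and its scope, and nothing excludes pairs.

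The denominator is also inferred. Birth totals are collected, and the plan marks a treated-only population where it clearly wants one. This too stands, which is why the point is conditional.

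Association among treated infants is, moreover, a legitimate quantity, and the +0.47 example shows that the all-births table has its own built-in association. Replacing one test by the other is therefore no remedy.

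A reader might go further and infer that the both-absent cell is cut off altogether, or that every unrelated or positively related pair will come out significantly negative. The document does not support that. Infants who enter through a third item stay in the cell (480 in the 4% and 5% example), and the rare pairs whose frequencies the article gives can behave otherwise. Extreme illustrations, such as two items at 6% with 2% joint, leave the cell empty only because 6 + 6 - 2 = 10% uses up the whole treated rate.

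**Conclusion.** The concern holds in a limited form. If phi and chi-square are run for intervention pairs on the individual records, which the wording permits and the database makes the easy default, phi for unstarred pairs is biased downward. For common items the bias is large: -0.735 instead of 0 for an independent 4% and 5% pair. A moderate positive association reverses sign when joint use is below about 10 times chance at the planned 10% treated rate. Strongly linked rare pairs keep their sign, and unrelated very rare pairs are not significant.

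These sizes rest on expected counts at the planned totals, on assumed frequencies for every item other than ventilation, compressions and adrenaline, on assumed joint frequencies, and on no clustering by hospital. The frequency estimates and the subgroup comparisons in Table 2 are outside this point.

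**What to change.** In Data analysis:

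1. Limit phi and the chi-square test to factor-by-intervention comparisons.
2. For pairs of interventions, report co-occurrence percentages with 95% confidence intervals, labelled *among infants receiving at least one intervention*, without a test of independence.
3. If an all-births association is also shown for unstarred items, rebuild the both-absent cell as total births minus included infants with either item, name that denominator, and note that shared need for support alone produces a positive association.
4. Keep suction and peripheral IV access conditional and descriptive only.

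The cost is a few sentences and a few lines of R; the monthly birth totals are already collected. The downside is that intervention pairs carry no p-values. An all-births version by gestational age is not possible, because births are not counted by gestational age.
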